### Secondary objectives

- To evaluate repeatability, sensitivity and specificity of the LiveOCT device.
- To evaluate costs and consequences- from an NHS perspective we will explore the costs and consequences of the LiveOCT device as compared to usual care.
- To study patient experience on LiveOCT device.

1. Study design

This study will follow a prospective observational study design. The single study site is St. Paul’s Eye Unit, The Liverpool University Hospitals NHS Foundation Trust (LUHFT).

Following recruitment, eligibility assessments and consent, participants will undergo a baseline assessment. Follow up assessments will take place after 3 and 6 months.

During each visit, the participant will undergo standard eye examinations (visual acuity and slit-lamp bio microscopy), and non-invasive tests including endothelial cell counting (ECD), tomography, and OCT imaging by standard OCT devices (TOMEY CASIA SS-1000 and Heidelberg Spectralis) and our new LiveOCT device variants (D1 and D2). Two qualified individuals, both operating one of two LiveOCT devices equipped with the study software, will perform the study device measurements. Each patient will be measured three times with each device at both the baseline and at follow-up visits (after 3 and 6 months). See figure 1 for the study design showing the study design/ patient pathway.

We expect the duration of D1 and D2 assessments (capturing 3 images on each device per visit) to take 15 minutes for each device, so 30 mins in total will be dedicated to our novel OCT devices each visit. The order of the OCT devices will be randomised using a random permutation approach to avoid bias through patient or investigator fatigue but the all measurements on each device will take place at the same time as to avoid delays caused by positioning the patient.

   
[figure not shown]

Figure 1. Schematic of the Study design/ patient pathway

1. Study setting

The Study will run in a single site at the Clinical Eye Research Centre (CERC) in St. Paul’s Eye Unit within The Liverpool University Hospitals NHS Foundation Trust (LUHFT).

1. Study participants

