## Baseline and subsequent assessments

For each participant, there will be 3 visits: baseline, month 3 and month 6. During each visit, the participant will undergo standard eye examinations (visual acuity and slit-lamp bio microscopy), and non-invasive tests including endothelial cell counting (ECD), tomography, and OCT imaging by standard OCT devices (TOMEY CASIA SS-1000 and Heidelberg Spectralis) and our new LiveOCT device variants. Two qualified individuals, both operating one of two LiveOCT devices equipped with the study software, will perform the study device measurements. Each patient will be measured three times with each device at both the baseline and at follow-up visits. A questionnaire will be completed on their experience and view of the device at the end of each visit.

The following procedures will be carried out on each patient at baseline, month 3 and month 6, as shown in Table 1:

1. Eye examinations (visual acuity and slit-lamp bio microscopy)
2. Endothelial cell counting (ECD) with confocal microscopy
3. Tomography with Pentacam camera
4. OCT imaging with devices currently in clinic (The TOMEY Casia and Heidelberg Spectralis)
5. Imaging by our new LiveOCT device – variant 1 (D1) and 2 (D2)
6. Patient experience questionnaire

The order of the OCT devices will be randomised using a random permutation approach to avoid bias through patient or investigator fatigue but the all measurements on each device will take place at the same time as to avoid delays caused by positioning the patient.

All the procedures except for imaging with our new LiveOCT device are part of standard care. For patients with keratoconus, all the three visits are standard patient care pathway. For patients with FECD, month 3 visit is an additional visit to the standard care. For healthy volunteers, all the 3 visits will be research activities.

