## Sample size calculation

The current gold standard for measuring the cornea is based on the tomographic images of the Pentacam for the thinnest corneal thickness (TCT). There is insufficient evidence in the literature to determine what change might occur in Bowman’s layer longitudinally. Bowman’s layer has not been measured before using a Pentacam so that we do not have a comparison. The primary endpoint, therefore, is a change in TCT. We do not know whether the change in TCT will be reflected in a change in Bowman’s layer and or Descemet’s membrane thickness and therefore we are not able to use the changes in these layers to determine the sample sizes. The changes in Bowman’s layer and Descemet’s membrane will be exploratory but we expect that changes will occur as TCT changes. For TCT, using a Pentacam, the cut-off for a change in TCT is 12.1um between the mean of three measurements on 2 occasions (Brunner et al, 2018). We expect the LiveOCT to detect all patients who have this change, that is, >12.1um in TCT. The incidence of patients with keratoconus (KC) changing over a 6 month period is expected to be 20% using the Pentacam. Therefore 8 of the 40 patients included will be expected to show this change using the Pentacam. Based on the increased resolution of the Liverpool LiveOCT we expect a much greater sensitivity for detecting change in TCT. We estimate that 50% of patients will show a change that we can detect based on the increased resolution of 2μm of the LiveOCT compared to 20μm of the Pentacam. Evidence for the current OCT performed worse than the Pentacam (Brunner et al) hence the choice of the Pentacam as a comparison for TCT. A difference, therefore, of between 20% and 50% would require a sample size of 36 with an alpha of 0.05 and beta 0.2. Given that over the course of the study 10% will drop out we calculate a sample size of 40 patients with KC. For patients with FECD, we do not have data on the change in TCT, however, extrapolating from patients with KC the change in TCT is usually greater in FECD hence a similar or slightly smaller sample size is needed which we estimate to be 30 patients. For healthy subjects we do not expect the change in TCT to be greater than the 95% TCT cut-off 8.81um (Pentacam) over the course of the study, based on Brunner et al 2018. We, therefore, expect 20 subjects in this group to provide reproducibility data using the LiveOCT.

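### The keratoconus sample size of 36 matches a two-independent-groups formula, but the design is paired, so the stated 80% power fits neither the design nor the protocol's own overlap assumption

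*Protocol*

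**What the plan says.** Sample size calculation (13.1) takes change in thinnest corneal thickness (TCT) as the primary endpoint for sizing. For the Pentacam: "The incidence of patients with keratoconus (KC) changing over a 6 month period is expected to be 20% using the Pentacam". For LiveOCT: "We estimate that 50% of patients will show a change that we can detect based on the increased resolution". From these two proportions it concludes: "A difference, therefore, of between 20% and 50% would require a sample size of 36 with an alpha of 0.05 and beta 0.2". It then allows for losses: "Given that over the course of the study 10% will drop out we calculate a sample size of 40 patients with KC". No test, formula or discordance rate is given.

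Two further statements in the same section bear on how the classifications relate. The Pentacam changers are counted inside the enrolled group: "Therefore 8 of the 40 patients included will be expected to show this change using the Pentacam". LiveOCT is expected to pick up all of them: "We expect the LiveOCT to detect all patients who have this change, that is, >12.1um in TCT".

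Overall description of study participants gives a single keratoconus group of 40. Baseline and subsequent assessments lists the procedures that each patient has at baseline, month 3 and month 6. The list includes "Tomography with Pentacam camera" and imaging on both LiveOCT variants.

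**The concern.** Every keratoconus patient supplies both a Pentacam result and a LiveOCT result. Comparing 20% with 50% is therefore a within-patient comparison of two correlated yes/no classifications. Its power is governed by the discordant patients: those called changed by LiveOCT only and those called changed by the Pentacam only. The two marginal percentages fix the difference between these cells (0.30) but not their sizes.

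A calculation that uses only the two margins and treats them as coming from different people answers a question about another design. At stake is whether the stated beta of 0.2 means anything for this study. This is the protocol's only power calculation. The FECD group of 30 is also argued by extrapolation from the keratoconus group, so the weakness carries over to it.

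**Working it through.** **Inputs, all from 13.1:** Pentacam proportion 0.20; LiveOCT proportion 0.50; alpha 0.05 (sidedness not stated); beta 0.2; stated size 36; dropout 10%.

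**Step 1: reproduce 36.** For two independent proportions with unpooled variance, two-sided:

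n per group = (1.960 + 0.842)² × (0.20 × 0.80 + 0.50 × 0.50) / 0.30² = 7.849 × 0.41 / 0.09 = 35.76, rounded up to 36.

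This is a per-group figure, so that design would have 2 × 36 = 72 patients. Other common versions do not give 36:

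| Method | n |
|---|---|
| Two groups, pooled, two-sided | 39 per group (45 with continuity correction) |
| Two groups, arcsine, two-sided | 38 per group |
| Two groups, pooled, one-sided | 31 per group (37 with continuity correction) |
| Two groups, unpooled, one-sided | 29 per group |
| One sample against a fixed 20%, two-sided | 17 (normal) or 19 (arcsine) |

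**Step 2: dropout.** 36 / (1 − 0.10) = 40. This reproduces, and it shows that 36 was taken as the whole keratoconus sample.

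**Step 3: the paired calculation under the protocol's own overlap.** If LiveOCT detects every Pentacam changer, Pentacam-only = 0 and LiveOCT-only = 0.50 − 0.20 = 0.30. All discordant patients then favour LiveOCT. With m discordant patients, all in one direction, the exact two-sided McNemar p-value is 2 × 0.5^m. That is 0.0625 for m = 5 and 0.03125 for m = 6, so the test rejects when m ≥ 6.

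- 36 completers: P(Binomial(36, 0.30) ≥ 6) = 97.8%.
- 25 completers: P(Binomial(25, 0.30) ≥ 6) = 80.7%. With 24 it is 77.1%, so 25 is the smallest number that reaches 80%.
- The normal approximation, n = (1.960√p_d + 0.842√(p_d − d²))² / d² with p_d = 0.30 and d = 0.30, gives 23.66, so 24 pairs. It puts power at 36 at about 94%.

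**Step 4: sensitivity to the overlap.** The difference stays at 0.30. Apart from the first row, these cases are assumptions of this review and depart from the protocol's expectation. The test is exact two-sided McNemar.

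| LiveOCT only / Pentacam only | Meaning | Power at 36 | Completers for 80% |
|---|---|---|---|
| 0.30 / 0 | LiveOCT detects all Pentacam changers (protocol) | 98% | 25 |
| 0.35 / 0.05 | LiveOCT detects 75% of them (0.15 of 0.20) | 81% | 36 |
| 0.40 / 0.10 | Devices classify independently (0.50 × 0.80; 0.20 × 0.50) | 69% | 46 |
| 0.50 / 0.20 | No overlap | 51% | 64 |

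Power at 36 is close to 80% only when Pentacam-only changers are about 5% of patients (exact test) to 7% (normal approximation). Neither figure appears in the protocol, and both contradict its expectation that there are none.

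**The case against.** **The formula is inferred.** The protocol names no method, and a paired calculation can also reach 36: the exact test at 0.35/0.05, or the normal approximation at 0.37/0.07 (35.92). This stands, so the claim is that 36 matches the independent-groups formula, not that it can arise no other way. It does not rescue the sentence, because those paired routes need LiveOCT to miss some Pentacam changers and the same section expects it to miss none.

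**The error is conservative on the protocol's own terms.** This also stands. Under the stated overlap, 36 completers are more than enough. A reader might infer from the 72 that the study is half the size it needs, but 72 belongs to a design with separate device groups, which this study does not have.

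**No invalid test is planned.** A reader might infer that the analysis will treat the two devices' results as independent samples. Statistical analysis plan (13.2) does not say so. Its examples are Bland-Altman analysis, coefficients of variation, a random-effects model with operator and eye, and sensitivity and specificity; none is an unpaired comparison of proportions. The test for this contrast may properly be left to a separate analysis plan. What that plan cannot repair is a completed calculation in the protocol whose inputs do not give its result for this design.

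**Conclusion.** The point holds as a wrong method and a misstated power, and it should be fixed. The figure of 36 with beta 0.2 fits neither the paired design nor the protocol's stated overlap. Under that overlap, power at 36 completers is about 98% and 25 would do.

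The documents do not show the study to be too small. With the exact test, power at 36 falls below 80% only if Pentacam-only changers exceed roughly 5% of patients. The 81%, 69% and 51% figures are sensitivity cases, and the 69% for independent classification is not a lower bound.

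All results rest on the protocol's 20% and 50%, a two-sided alpha of 0.05, 36 completers and an exact McNemar test. The figures shift with the version of the test: the normal approximation gives about 94%, 84%, 74% and 58% for the four cases.

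**What to change.** Replace the sample-size sentence in 13.1 with a paired calculation, for example:

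*The proportions of keratoconus patients classified as changed by LiveOCT and by the Pentacam will be compared within patient (exact two-sided McNemar test, alpha 0.05). Assuming that LiveOCT detects all Pentacam changers (discordant proportions 0.30 and 0), 36 completers give 98% power. If this assumption does not hold, power is 81% for 0.35 and 0.05, 69% for 0.40 and 0.10 (independent classification), and 51% for 0.50 and 0.20 (no overlap). Allowing for 10% dropout, 40 patients will be enrolled.*

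Naming the test in this sentence is enough; 13.2 need not change. The cost is a few sentences of text. Enrolment stays at 40, and no visits or procedures change.

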## Statistical analysis plan

Statistical analysis will be performed as appropriate using SPSS version 20.0 (SPSS IBM, Chicago, IL, USA). For example, the Bland-Altman analysis will be used to visualise agreement, the coefficients of variation (CV) analysis will be performed to assess repeatability and reproducibility, and two-way random effect ANOVA model (REML) will be used to assess the random effects operator (confounded with device) and eye for the measured endpoints were within the specified range for this device. Sensitivity and specificity tests will be performed.

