Optical coherence tomography (OCT) has been widely used in the management of eye disease. Commercially available OCT systems are still unable to meet the increasing demand posed by clinical decision-making. With an i4i grant, we have in Liverpool invented a new OCT device. This has enabled us to achieve in vitro in human corneas an improved resolution down to 2.1 microns. While the OCT device worked well in its current form in the laboratory, we were to yet translate this application into clinical practice and potentially provide benefit to patients. This translation required relevant in vivo device optimisation and improvement as well as clinical studies to demonstrate its potential to help improve the management of ophthalmic diseases.

1. Rationale

In our current i4i project (Ref: II-LA-1116-20008), we are planning to address this by realising a novel clinically proved OCT device that makes use of new technologies and approaches that can be used on human subjects. Having designed and built the device, we hope to evaluate and optimise the device and data analysis on both healthy volunteers and patients with various cornea diseases. The project will ultimately bring significant benefits for people with eye disease, improving healthcare, and subsequently reducing social and economic costs. We have developed a proof-of-concept observational study protocol to demonstrate clinical utility for diagnosis, disease classification and management. We will examine the performance of our LiveOCT device with comparison to current clinically used devices (corneal topography and tomography devices including OCT and ultrasound) with particular regard to intra, inter-observer and inter-device variability. This will be used to determine precision and accuracy, the latter based on currently accepted clinical standards. In comparison with other standard techniques, we hope to identify the uniqueness of our LiveOCT for supporting improved diagnosis, monitoring and treatment of eye diseases. We have developed 2 slightly different variants of our LiveOCT device, device 1 (D1) and device 2 (D2). The only difference between the variants is a very slight modification of the internal optics, which results in different image properties. There will be no difference in operation or patient experience between the variants.

1. Objectives and outcome endpoints/measures

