## Secondary outcomes

**Repeatability/reproducibility:** Outcome metrics will be the repeatability and reproducibility of measurements (identification and thickness) of structural parameters of the cornea, corneal surface contour and refractive power.

**Sensitivity and specificity:** We will use published grading systems specific to the two main conditions of FECD and keratoconus. For keratoconus, the sensitivity of the LiveOCT will be assessed by its ability to detect the same diagnostic parameters of non-uniform and focal corneal thinning and irregular and non-asymmetric anterior and posterior corneal profiles currently measured using the Pentacam. For FECD, the sensitivity of the LiveOCT will be assessed by its ability to measure increases in corneal thickness and areas of corneal swelling, and excrescences (guttata) and thickening of Descemet's membrane in patients who have guttata evident with slit lamp bio microscopy and increased corneal thickness measured with the Pentacam. Specificity will be defined as the percentage in which the described diagnostic changes in the cornea for keratoconus and FECD are not apparent with the LiveOCT device.

**Patient experience:** Study participants will be asked to fill in a simple set of questions concerning their experience with the LiveOCT devices. The patients will be asked to fill out paper copies of the questionnaire after the end of each study appointment, but the study nurse will be available to help if required.

If the participant indicates that they are feeling particularly anxious or depressed on the questionnaire, a member of their care team will pass this information onto their GP.

**Cost Effectiveness:** See 13.3 - economic evaluation

1. Definition of end of study

The study will be completed and terminated on 31st October 2022, which is defined to be the date when analysis of the data collected during the trial is being completed.

Suspension or early termination of the study when there are serious concerns about subjects’ safety and inadequate performance, that cannot be mitigated by modifications of the study protocol based upon the review of the safety data.

1. Discontinuation/ withdrawal of participants from study treatment

If a decision is made by the participant and or/clinician not to continue with the study, the participant will be removed from it and the event recorded. Data will still be collected unless the participant explicitly withdraws consent for it.

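### One operator per LiveOCT variant: the combined operator-and-device effect measures neither inter-observer nor inter-variant variability, so LiveOCT reproducibility cannot be attributed to either

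*Protocol*

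**What the plan says.** **Allocation.** The Study design section and Baseline and subsequent assessments use the same sentence: "Two qualified individuals, both operating one of two LiveOCT devices equipped with the study software, will perform the study device measurements". Replication is stated as "Each patient will be measured three times with each device at both the baseline and at follow-up visits". On randomisation, the protocol says: "The order of the OCT devices will be randomised using a random permutation approach". Neither section randomises, rotates or crosses the operators.

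**Model.** The Statistical analysis plan section offers, among its example methods, a "two-way random effect ANOVA model (REML) will be used to assess the random effects operator (confounded with device) and eye".

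**Purpose.** The Rationale says LiveOCT performance will be examined "with particular regard to intra, inter-observer and inter-device variability". Under Secondary outcomes: "Outcome metrics will be the repeatability and reproducibility of measurements (identification and thickness) of structural parameters of the cornea". The Sample size calculation section includes the 20 healthy subjects in order to supply LiveOCT reproducibility data.

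**The variants.** The Rationale states: "The only difference between the variants is a very slight modification of the internal optics, which results in different image properties". It adds that operating them, and the patient's experience of them, is the same.

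**The concern.** Merging operator and device into one effect might be tolerable if the two units were nominally identical, because the device share would then be only unit-to-unit noise. Here the protocol itself expects a real difference between the units. The merged component therefore contains a deliberate optical difference plus whatever separates two people's technique, and it answers neither question.

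Two things are at stake. First, a reproducibility figure for LiveOCT could not be read as how much results vary between users, which is what a clinic adopting the device would want to know. Second, if one variant looked better or worse than the other, directly or in its agreement with the Pentacam, Casia or Spectralis, the team could not tell optics from operator. They could carry forward a variant because of the person who ran it. No later analysis can recover the separation, because the two factors never vary independently in the data.

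**Working it through.** The plan gives no figure on this point. Its one calculated figure, the keratoconus sample size, does reproduce: (1.960 + 0.842)² × (0.2×0.8 + 0.5×0.5) / 0.3² = 35.76, so 36, and 36/0.9 = 40. The present point does not touch it.

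**Inputs from the protocol.** 90 participants; 2 LiveOCT variants; 2 operators, one per variant; 3 replicates per variant per visit. **Assumption:** one eye per participant, for counting rows only. The result does not depend on it.

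**Step 1, the design as written.** Operator A always runs D1 and operator B always runs D2. Rows per visit: 90 × 2 × 3 = 540. The columns are intercept, operator and device. The operator and device columns are identical, so the rank is 2 of 3.

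**Step 2, the same in variance terms.** Two measurements share an operator exactly when they share a device. The covariance patterns generated by a random operator effect and a random device effect are therefore the same matrix. REML can estimate only var(operator) + var(device). More eyes, replicates or visits add rows with the same pattern and do not help.

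**Step 3, the mean difference.** Write V for the true D1-minus-D2 difference from optics and O for the A-minus-B difference from operators. Every participant's D1-minus-D2 difference has expectation V + O. Nothing in the data splits that sum.

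**Step 4, what survives.**
- Repeatability: the three replicates share eye, visit, device and operator, so the offset drops out of their spread.
- Change over time: if the same operator stays on the same variant, a constant offset appears in both the baseline and the month 6 value for an eye, and (change + offset) − offset = change.

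**Step 5, pairing randomised between participants, no extra scans.** In half the participants A runs D1 and B runs D2, with expected difference V + O. In the other half the roles are reversed, with expected difference V − O. Then:
- the average of the two group means is [(V + O) + (V − O)]/2 = V;
- half their difference is [(V + O) − (V − O)]/2 = O.

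Rows per visit remain 540 and the rank is 3 of 3. A full crossing, with both operators on both variants in everyone, also gives rank 3 of 3 but needs 90 × 4 × 3 = 1,080 scans per visit.

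**Step 6, precision.** Let s be the SD of a participant's D1-minus-D2 difference within a pairing group, with n participants split equally. The variance of the estimate of V is ¼ × [s²/(n/2) + s²/(n/2)] = s²/n. That equals the variance of the uncrossed mean difference, so separating the two effects loses no precision on V.

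**The case against.** **The protocol discloses the confounding, and this is a proof-of-concept observational study.** True, and it bears on severity. Disclosure does not make the combined component interpretable as reproducibility between observers.

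**The allocation sentence is loosely worded.** Read alone, it could allow both people to use both units. The parenthesis in the model description settles the reading as one operator per device. If operators are in fact meant to rotate, the model description is wrong and needs changing instead.

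**The aim sits in the Rationale, and its inter-device part may mean LiveOCT against the commercial instruments.** Both stand. The numbered secondary objectives list repeatability but not inter-observer variability. The point therefore rests on the inter-observer aim and the reproducibility outcome, not on a stated D1-versus-D2 variability aim.

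**Stronger readings that the document does not support:**
- *That the primary comparison is confounded because it is D1 against D2.* The Study summary, Primary objective and Primary outcomes set the variants against existing devices. No D1-versus-D2 test is listed.
- *That real progression will be reported as poor repeatability, or that fellow eyes will be counted as independent.* These need visits to be pooled or both eyes to be analysed, and the protocol states neither. The model is introduced as an example, and an SAP could settle both points.
- *That the imprecision of a two-level variance measures the defect.* On 1 degree of freedom the 95% limits for a variance run from about 0.2 to 1,018 times the estimate. That comes from having only two levels and would apply to two perfectly crossed operators as well. It is a reason to report operator as a contrast, not a measure of the confounding.

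**Conclusion.** The point holds in this limited form. Under the stated allocation, operator and variant are not separable at any sample size (rank 2 of 3). The LiveOCT reproducibility outcome and the inter-observer aim cannot be attributed to observer or device, and any observed difference between D1 and D2 mixes optics with operator.

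The size of the bias cannot be given, because the protocol states no operator or optical difference. The observed contrast is V + O with O unknown. Each variant's agreement with the standard instruments can still be described, but only as that variant in that operator's hands.

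The conclusion assumes one operator per variant throughout. The cancellation in within-eye change also assumes that the offset is constant over the six months.

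This should be fixed but does not invalidate the study: it affects part of a secondary outcome, and both same-visit repeatability and longitudinal change are preserved. It needs a design change, because an SAP cannot separate factors that were never crossed.

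**What to change.** 1. **Study design, and Baseline and subsequent assessments:** randomise the operator-to-variant pairing per participant, preferably balanced within each of the three groups, and keep that pairing for all of the participant's visits. Do not swap operators between visits, because that would add operator noise to the six-month change in corneal thickness. Record the actual operator for every scan.
2. **Statistical analysis plan section:** fit variant as a fixed effect, since D1 and D2 are two specific designs and not a sample of devices. Add a separate operator term, reported as an estimated contrast because there are only two operators, and keep eye as random. Report the D1-D2 bias with its confidence interval.
3. **If operators cannot be crossed:** withdraw the claim to assess inter-observer variability and report the component only as combined operator-plus-variant.

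**Cost.** Both operators must be trained on both variants, and an allocation list must be kept. The Rationale says the variants operate identically, so the training burden should be small. No extra scans, staff or visits are needed.

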## Overall description of study participants

90 subjects 12 years old and above who meet the inclusion and exclusion criteria will be recruited and subsequently tested at the cornea clinics of St Paul’s Eye Unit (SPEU), LUHFT. There will be 3 groups of participants: 40 patients with keratoconus, 30 with FECD and/or corneal lamellar surgery, and 20 with no known corneal abnormality.

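### The operator/device random effect in section 13.2 has only two levels, which are two deliberately different optical variants, so its variance cannot support a statement about inter-device variability or about a specified range

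*Protocol*

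**What the plan says.** The Protocol's Statistical analysis plan (section 13.2) offers three methods by way of example. Bland-Altman is for agreement: "the Bland-Altman analysis will be used to visualise agreement". Coefficients of variation are for repeatability and reproducibility. The third method is the one at issue: a "two-way random effect ANOVA model (REML) will be used to assess the random effects operator (confounded with device) and eye". The same sentence then runs on: "eye for the measured endpoints were within the specified range for this device". The grammar is broken, no numerical range is given and no acceptance rule is stated.

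The Study design section fixes the number of levels: "Two qualified individuals, both operating one of two LiveOCT devices equipped with the study software, will perform the study device measurements". The section on baseline and subsequent assessments repeats this. Replication is also fixed: "Each patient will be measured three times with each device at both the baseline and at follow-up visits".

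The Rationale describes the two devices: "The only difference between the variants is a very slight modification of the internal optics, which results in different image properties". The description of the study intervention says the same in substance. The Rationale also makes variability between observers and between devices part of the study's purpose, to be used in establishing precision and accuracy.

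The participants are "40 patients with keratoconus, 30 with FECD and/or corneal lamellar surgery, and 20 with no known corneal abnormality", 90 in all.

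**The concern.** A random effect treats its levels as draws from a population and estimates the variance of that population. Here there are two levels, and they were not drawn from anything: D1 and D2 were built to differ. The variance of a population of devices is not what two designed variants can estimate. Even if it were, two levels give one degree of freedom. Adding eyes, captures or visits sharpens each device's mean but does not add levels.

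Any conclusion on inter-device or inter-operator variability drawn from this component would rest on almost no information. The same holds for any claim, drawn from it, that measurements lie within a specified range. Yet the paired data can estimate the difference between the two operator-device pairs closely, and section 13.2 does not mention that estimate.

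**Working it through.** **The plan's own figure.** The Protocol gives none for this assessment. Its only calculation is the sample size: "A difference, therefore, of between 20% and 50% would require a sample size of 36 with an alpha of 0.05 and beta 0.2". This reproduces with the formula for two independent proportions and unpooled variance: (1.960 + 0.842)² × (0.2×0.8 + 0.5×0.5) / 0.3² = 35.8, so 36, and 36/0.9 = 40. It has no bearing on the point here.

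**Inputs.** Operator-device levels J = 2 (Study design). Three captures per device per visit (Study design). 90 participants (description of study participants). For thinnest corneal thickness (TCT), Pentacam cut-offs for change of 8.81 µm in healthy eyes and 12.1 µm as the general cut-off (Sample size calculation).

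**1. Degrees of freedom.** With J levels and many eyes, the estimated between-level variance is approximately σ² × χ²(J−1)/(J−1). For J = 2 this is σ² × χ²(1), whatever the number of eyes.

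**2. Confidence interval for the SD on 1 df.**
- Lower factor: √(1/χ²(0.975; 1)) = 0.446.
- Upper factor: √(1/χ²(0.025; 1)) = 31.9.

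The two-sided 95% interval therefore runs from about 0.45 to 32 times the estimated SD.

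**3. Illustration only: comparing the point estimate with a limit.** The Protocol states no such rule. Let r be the true SD of the operator/device component divided by the limit. Then P(estimate below limit) = P(χ²(1) ≤ 1/r²).

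| r | Probability |
|---|---|
| 1 | 0.683 |
| 1.5 | 0.495 |
| 2 | 0.383 |

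Simulating the balanced design with 20 to 90 eyes and three captures gave 0.49 to 0.50 at r = 1.5 when the residual SD was at or below the limit. It gave up to about 0.55 with 20 eyes and a residual SD five times the limit. More levels would help: at r = 1.5 the probability is 0.359 with 3 levels, 0.223 with 5 and 0.089 with 10.

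**4. The same illustration if the range applies to the total reproducibility SD** (operator/device plus residual; 40 eyes, three captures, true total 1.5 times the limit).

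| Operator/device share of variance | Probability estimate is below limit |
|---|---|
| 25% | about 0.00 |
| 50% | 0.03 |
| 75% | 0.39 |
| 100% | 0.49 |

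**5. Would a confidence bound on the component rescue it?** The one-sided 95% upper factor is √(1/χ²(0.05; 1)) = 15.9. A true SD at the limit would then pass 5% of the time, and one at 1.5 times the limit about 3%. But a true SD at one fifth of the limit would pass only about 25% of the time, and one at a tenth about 47%. False acceptance is controlled, at the price of very little chance of showing conformity.

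**6. What a fixed contrast would give for TCT.** The Protocol gives no SD for the D1−D2 difference. Assume one paired difference per participant, with an SD between 8.81/1.96 = 4.5 µm and 12.1/1.96 = 6.2 µm. This borrows Pentacam change data and treats both cut-offs as 1.96 SDs. The half-width is 1.96 × SD/√n:
- n = 90: 8.81/9.487 = 0.93 µm to 12.1/9.487 = 1.28 µm.
- n = 81 (10% dropout applied to all groups): 8.81/9 = 0.98 µm to 12.1/9 = 1.34 µm.

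**7. Why those cut-offs cannot also be the limits for a mean difference.** They are thresholds for change in an individual eye. If the whole interval had only to lie inside ±8.81 µm, a mean offset of 8.81 − 0.93 = 7.9 µm would still be accepted. With ±12.1 µm, it would be 12.1 − 1.28 = 10.8 µm. The Protocol's argument for the device rests on a resolution of 2 µm.

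**The case against.** The strongest reply is that section 13.2 is illustrative and its sentence garbled. It states no decision rule, and the range is attached to the measured endpoints, not to the variance component. A limit, a confidence bound and an acceptance rule may all be in a separate statistical analysis plan that is not shown. All of this stands.

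It rules out a tempting stronger reading: that a device spread 1.5 times too large would be passed about half the time. That figure needs a point-estimate rule the Protocol does not contain, and it applies to the operator/device component alone. On total reproducibility SD the figure runs from near 0 to about 0.5.

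Two further inferences also fail. A reader might conclude that all the precision and agreement aims rest on this statistic. They do not: coefficients of variation and Bland-Altman analysis are named for those aims, and the eye and residual components draw on many eyes and repeat captures. A reader might also conclude that conformity could never be shown from two levels. With a bound it could, though with poor power.

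The confounding is disclosed, and repeatability and reproducibility are secondary outcomes.

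The reply does not remove the modelling point. The Protocol itself fixes both the random effect and the two levels. A threshold supplied elsewhere would not add a degree of freedom or turn two designed variants into a sample.

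**Conclusion.** The point holds as a modelling defect. The operator/device variance component has 1 degree of freedom by design, and its SD is known only to within about 0.45 to 32 times the estimate. It should not be the basis for any statement about inter-device or inter-operator variability or about a specified range. This conclusion depends only on the model and the two levels stated in the Protocol. It does not depend on the absence of a limit or rule, which is not a finding here.

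The 50% figure is an illustration under an assumed rule and should not be quoted as a property of the plan. The half-width of 0.9 to 1.3 µm rests on an SD borrowed from Pentacam change data and on one paired difference per participant. The LiveOCT devices' own SD may differ.

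**What to change.** In section 13.2:

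- Keep eye as a random effect and fit D1 versus D2 as a fixed effect.
- Report the mean D1−D2 difference with its 95% confidence interval, described as the difference between these two operator-device pairs.
- Base any within-range statement on that interval and not on the two-level variance component.
- Set any limit for the mean difference before analysis and justify it as a limit for mean bias. Do not use 8.81 µm or 12.1 µm for this purpose.
- Estimate repeatability from the residual (repeat-capture) variance within each device.

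The cost is analysis wording only; the data collected do not change. The downside is that conclusions apply to these two operator-device pairs alone, and operator and device remain inseparable. Separating them would need operators crossed with devices, and a usable variance component would need more operators. Both are design changes.
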